## Abstract

E-Health childhood obesity treatment interventions may serve as favorable alternatives to conventional face-to-face programs. More studies are needed to evaluate the effectiveness of such interventions beyond immediately post-program completion, including exploring program features impacting effectiveness. This randomized controlled trial with a qualitative component and waitlisted control group will evaluate the effectiveness of a 10-week family-focused e-Health program for school-aged children with overweight/obesity and explore the experience of families completing the program. The primary outcome is the change in BMI z-score and will be assessed from baseline to 10 weeks. Secondary outcomes include (the change in) waist circumference, dietary intake, physical activity, quality of life, and experiences, and will be assessed at baseline, post-10 weeks, and/or immediately, 3-, 6-, and/or 12-months post-program completion. Independent *t*-tests will be used to compare the differences in means and analyses of variances (ANOVAs) will be conducted to investigate the impact of the program or of being waitlisted and the effect size of the program on quantitative outcome measures. Reflexive thematic analysis will be used with qualitative data. Findings from this study are expected to provide learnings to upscale conventional childhood obesity treatment services, in the hopes of curbing the rising rate of childhood obesity.

## 1. Introduction

Obesity remains highly prevalent worldwide, with an increased prevalence of school-aged children (aged 5–16 years) living with severe obesity [1,2,3,4,5,6,7]. Children with overweight and obesity, particularly in their earlier childhood years, are also more likely to become adults living with overweight and obesity [1,2,3,4,5]. The increasing rate of childhood obesity influences increased healthcare and living costs for individuals globally [5]. For instance, in Australia, obesity is the second-largest contributor to health costs, estimated to cost Australia $11.8 billion, and if obesity rates continue to increase, it will cost an additional $87.7 billion in 10 years’ time [8]. 

The historically high global obesity rate over the past decade is attributable to the high accessibility to and the promotion of energy-dense foods, and technological advancements that encourage sedentary activities [4,9]. For instance, based on Australia’s 2011–2012 National Nutrition and Physical Activity Survey, less than 1 in 4 children aged 5–14 years engaged in the recommended duration of physical activity (at least 1 h of physical activity with moderate to vigorous intensity) per day, including children older than 10 years being more likely to engage in insufficient levels of physical activity per day compared to children younger than 10 years old [10]. The World Obesity Federation’s 2019 childhood obesity atlas also reported that at least 60% of children aged 10 years and older in the 191 included countries engaged in less than the recommended duration of physical activity per day [11]. In Australia alone, only about 1 in 10 children undertake the recommended amount of physical activity and sedentary behaviors (no more than 2 h of at-leisure screen-based activities) and consume the recommended serves of fruits and vegetables per day [10,12,13,14]. As a progressive, chronic condition impacting growth, development, and the onset of non-communicable, high-cost diseases, urgent action is needed to address obesity during school-aged years [1,2,3,4,9,15]. 

Internationally, countries recognize the importance of improving obesity treatment [16]. For instance, in 2022, Australia proposed a National Obesity Strategy, including an aim to reduce the prevalence of children living with overweight and obesity, and to ensure that Australians living with overweight and obesity have access to health care services [9]. Treating childhood obesity, including providing accessible and effective treatment programs, also supports progress in achieving United Nations’ sustainable development goals [17]. Studies suggest that multicomponent, family-based, individualized programs that encourage behavior change are most beneficial in the treatment of childhood overweight and obesity, and are recommended by the National Institute for Health and Care Excellence (NICE) and the American Psychological Association (APA) [2,3,4,9,18,19,20,21,22,23,24,25,26,27,28,29,30,31]. Such services, however, are largely lacking worldwide or are costly [15,31]. Existing multicomponent, family-based lifestyle programs with multidisciplinary specialist input are conventionally administered in-person and/or in group-based settings, with strict eligibility criteria, to a limited number of families at a time and, thus, are inaccessible to many children and their families [2,9,16,18,32]. Such services were designed to be implemented on a scale smaller than the growing number of families with children with obesity needing treatment. These programs also have long waiting lists or are costly [16,32]. For instance, a 2019 survey of multicomponent, multidisciplinary pediatric weight management clinics in Australia identified 17 services that are largely located in metropolitan cities and had waiting lists of 12 months or longer [2].

Digitizing such programs or offering electronic health (e-Health) programs, is a promising alternative overcoming the limitations of conventional programs. E-Health is the delivery of health-related information and/or healthcare services in a digital format or platform, and may serve as a standalone or adjunct intervention to conventional healthcare interventions, delivered face-to-face [3,22,33]. E-Health interventions have been shown to improve the accessibility, efficiency, and efficacy of healthcare services and people’s sense of accountability to manage their own health [3,18,20,21,22,23,24,25,26,29,33,34,35]. The ubiquitous use of the internet, including by populations of low socioeconomic status and/or remote areas, further supports the adaptation of such programs. In 2018, it was reported that more than 97% of Australian families have access to the internet using at least one mode of technology [28].

E-Health programs may serve as a favorable alternative to in-person programs, including for children. Children are avid users of the internet, including accessing the internet for health-related advice and services [3,23,27,28]. Research also suggests that younger generations may prefer receiving and/or accessing information on behavior change through digital avenues [3,22]. For instance, adolescents who received nutrition and physical activity education online were better able to impact positive lifestyle changes compared to receiving the program in-person [36]. With excessive screen time being particularly common among young individuals, as well as influencing the manifestation of childhood overweight and/or obesity, the implementation of e-Health services may serve as a strategy to leverage the time spent on devices to deliver treatment services. 

There is a developing body of evidence examining the effectiveness of e-Health interventions for the treatment of children with overweight and/or obesity. A 2021 meta-analysis of 19 randomized controlled trials (RCT) found that e-Health childhood obesity interventions significantly reduced BMI z-score (mean difference −0.063, Z = 4.66, *p* < 0.001) in children aged 3 to 16 years [3]. Similarly, a 2022 rapid review of 23 studies showed that family-based behavioral change e-Health programs in primary-school-aged children were able to significantly impact weight-based outcomes or lifestyle behaviors and/or habits [37]. This body of evidence, however, is largely limited to short-term program efficacy (i.e., immediately post-program with or without follow-up at 6 months or less), is parent- or child-focused as opposed to family-focused, and predominantly measures program effectiveness based on changes in weight-based outcomes [3,22,37]. These studies have also largely focused on e-Health programs delivered as adjunct interventions to conventional healthcare interventions delivered face-to-face. With the increased demands of healthcare services and drive for the delivery of remote services during the COVID-19 pandemic, more studies on interventions delivered predominantly via e-Health modalities vs. e-Health programs as adjuncts to conventional treatment services are needed to improve childhood obesity treatment programs.

Since the COVID-19 pandemic, healthcare systems have adopted online services and are committed to develop e-Health interventions for the prevention or treatment of diseases, including obesity [3,38]. The interest, preferences, and/or expectations of program end-users influence program uptake, use, and/or engagement; more studies exploring these outcome measures are needed, particularly to develop e-Health programs for the treatment of childhood obesity. As parents of school-aged children, particularly primary-school-aged children (aged 6–13 years), are recognized to greatly influence their child’s lifestyle behaviors and habits, exploring their perspectives of family-based lifestyle e-Health programs may inform program development [19,39]. Studies with this objective found that parents of early childhood and school-aged children, regardless of their socioeconomic status, prefer e-Health programs that involve the family unit, include evidence-based resources and interactive components, include individual support for families to set and achieve goals, focus on behavior change, are personalizable, and enable social support from other families completing the intervention [19,39]. Factors influencing a child’s engagement with a program may also differ from their parents’ perspectives; more studies exploring the child’s perspectives or experiences with e-Health interventions are, therefore, needed.

The online Better Health Program (BHPO) is a web-based program with health professional coaching sessions for the treatment of childhood overweight or obesity. The BHPO is the online adaptation of the in-person, group-based version, which is an evidence-based, family-centered lifestyle program for primary school aged children aged 7–13 years living with overweight or obesity, which has been successfully delivered and evaluated in Australia for over a decade. The in-person program is consistent with evidence-based guidelines on healthy eating, physical activity, and behavior changes [40]. An RCT evaluating the effectiveness of the face-to-face program demonstrated that it improved the degree of adiposity in children living with overweight or obesity, irrespective of whether families participated once or twice per week [40]. With changes related to the COVID-19 pandemic and digital culture encouraging a shift to e-Health modalities, the BHPO was developed. The web-based program is a 10-week multi-component e-Health program that involves weekly online modules/activity sessions educating on healthy eating, physical activity and behavior changes, weekly individualized phone calls with a health professional coach to support goal setting and program completion, the provision of supporting resources, and access to a closed Facebook group for the sharing of information and social support from other participating families. There has been no evaluation of the program in its online format. 

This protocol paper details the methodology of a study that aims to evaluate the effectiveness of a 10-week e-Health (web-based) healthy lifestyle program for primary-school-aged children aged 7–13 years (referred to hereon as “web-based program”). The primary aim of this study is to evaluate the effectiveness of a web-based program on the participating child’s health outcomes, including the impact of the web-based program on the child’s body mass index z-score (BMI z-score), waist circumference (WC), dietary intake, physical activity, and quality of life post-program-completion (immediately post-program, 6-months, 12-months). This study also aims to explore the experience of families completing a web-based lifestyle program.

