### 2.2. Study Design

This study is an RCT with a qualitative component and a waitlisted control group (Figure 1). This study is pragmatic in nature because it has been developed to evaluate the web-based program as it would typically be delivered. 

The 10-week web-based program will be administered by the administrating organization, Better Health Company (BHC), and is delivered during the year at primary school terms and midterms. In Australia, there are four school terms per year. The midterm programs will start approximately 6 weeks into the school term. Participants will be recruited for a school term or midterm program; a new recruitment cycle will begin, at the latest, 2 weeks prior to the commencement of the next earliest term or midterm program. Participants recruited during a school term or midterm recruitment cycle will only be considered for a school term or midterm program, respectively. Following study enrolment, participants allocated to the intervention group (Cohort 1) will complete the program in the subsequent commencing school term or midterm, whereas participants allocated to the control group (Cohort 2) will complete the waitlist control period in the next commencing school term or midterm. Participants allocated to the control group will not receive any intervention during the 10 weeks control period and will receive the (same) web-based program in the school term or midterm following the waitlist control term. Study involvement for each participant will run from baseline to 12-months post-program completion. 

Families who consent to the study will be randomized into the intervention or waitlisted control group. The randomization schedule was generated using block randomization (1:1 ratio) from Research Randomizer [41]. Group allocation will not be communicated to the BHC. Instead, study investigators will allocate participants to the respective school term or midterm in BHC’s data management system. In doing so, BHC’s health coaches, who are assigned to and have direct contact with families during the program, will be blinded to the study allocation.

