#### 2.3.2. Sample Size Estimation

The primary outcome will be the change in BMI z-score from baseline to 10 weeks. An a priori power analysis was conducted using G*Power version 3.1.9.4 [43] to estimate the sample size needed to detect a difference in the mean change in BMI z-score between the intervention and control group from baseline to 10 weeks using a *t*-test. The sample size estimation accounted for a possible reduction in BMI z-score within the control group, an effect size based on BHC’s pilot data, and a 30% attrition rate based on previous trials on a similar program (trials on the MEND program reported a 30% attrition) [44]. The effect size based on the change in BMI z-score and informed by pilot data was 0.6 (i.e., medium effect size using Cohen’s (1988) [45] criteria). With a 5% significance and 80% power, this study aims to recruit *n* = 118 participants (*n* = 59 intervention group; *n* = 59 control group) to observe a difference in the primary outcome measure between groups with this effect size using a *t*-test. 

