### 2.6. Outcome Measures

Outcome measures will be self-reported via surveys administered online, at baseline, post-program completion (10 weeks), and 6- and 12-months post-program completion. Participants allocated to the control group will be asked to complete an additional set of surveys following the 10 week control period. All study assessments will be administered online via a Research Electronic Data Capture (REDCap) [46,47] link, Australian Eating Survey (AES) [48], or Youth Activity Profile (YAP) [49] link, and distributed to participants via email.

Qualitative data will also be collected online through video conferencing and real-time transcribing platforms (Zoom [50], Otter.ai [51]) at 3 months post-program completion.

All study assessments, including study surveys and interviews, will be completed by both the participating child and parent/caregiver. All outcome measures will be self-reported by participants to complement the virtual nature of the intervention and include the participation of families from all geographic locations of Victoria. A study by Chai and colleagues supports the use of parent-reported measurements that are collected online for web-based lifestyle programs [52]. The study found that Australian parents of primary-school-aged children were relatively accurate in reporting their child’s anthropometric measurements, including their weight and height [52]. 

The primary outcome measure is the change in the child’s BMI z-score. Secondary outcomes include (the change in) the child’s BMI z-score, waist circumference, dietary intake, physical activity, quality of life, and the participating child and parent/caregiver’s experience of completing the program. Details on the collection of the outcome measures are summarized in Table 1.

The web-based program also includes surveys to be completed by participants as a part of the program activities. Data collected from these surveys may supplement data collected by study investigators, to inform outcome measures. 

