## 3. Discussion

Urgent action is needed to improve the treatment of childhood obesity. Few multidisciplinary weight management services currently exist for children outside the realm of primary health care, which, with limited resources, is predominantly focused on helping children with co-morbidities associated with weight and not the general population.

E-Health interventions are promising strategies for the treatment of childhood obesity. With modifiable risk factors, including engaging in excessive sedentary, digital-based activities, influencing the rising childhood obesity rates, family-focused e-Health treatment programs may serve as means to upscale conventional treatment interventions. Such programs may also adapt to the increased demands of healthcare services and (young) people’s way of living during the COVID-19 pandemic. 

Though there is a growing body of evidence suggesting the effectiveness of e-Health interventions for the treatment of childhood overweight and/or obesity, studies have largely focused on parent- or child-focused programs and short-term impacts on weight-based outcomes and/or lifestyle behaviors/habits [3,22,37]. Evidence on the specific components necessary for the successful uptake and effectiveness of family-focused e-Health treatment programs is also lacking [3,22]. This study’s methodology will add to the learnings of existing studies evaluating e-Health childhood obesity treatment programs, including addressing the aforementioned limitations [3,22,33]. This study also uses a strong design methodology; this study will use a waitlisted controlled, randomized trial, and is pragmatic in nature to deliver the intervention as it typically runs.

There are also strengths in the assessed intervention. This study involves a unique partnership between academics and industry to deliver a real-world family-focused e-Health intervention. The e-Health adaptation of the face-to-face, group-based program is expected to support family engagement; the web-based program includes elements expected from and favored by parents of children with overweight or obesity of (e-Health) childhood obesity treatment programs [19,39]. Program characteristics, including the web-based program’s mode of delivery, may also support program engagement from school-aged children with overweight or obesity themselves.

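### The primary aim promises effectiveness at 6 and 12 months after the program, but the only comparison with untreated children is at 10 weeks; later results are uncontrolled and should be labelled so

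*Protocol article*

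**What the plan says.** **Aim.** The Introduction states: "The primary aim of this study is to evaluate the effectiveness of a web-based program on the participating child’s health outcomes". It then lists BMI z-score, waist circumference, dietary intake, physical activity and, with the time points, "quality of life post-program-completion (immediately post-program, 6-months, 12-months".

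**Primary outcome and power.** Section 2.3.2 is narrower: "The primary outcome will be the change in BMI z-score from baseline to 10 weeks". The power calculation is for the between-group t-test of that change. The Abstract and section 2.7 agree with it, and the Abstract and section 2.6 list the other outcomes as secondary.

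**Control group.** Section 2.2: "Participants allocated to the control group will not receive any intervention during the 10 weeks control period". The same sentence goes on to say that controls "will receive the (same) web-based program in the school term or midterm following the waitlist control term".

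**Visits.** Section 2.6 schedules surveys "at baseline, post-program completion (10 weeks), and 6- and 12-months post-program completion", plus one extra set for controls at the end of the wait. Section 2.2: "Study involvement for each participant will run from baseline to 12-months post-program completion". Follow-up is therefore timed from each child's own program.

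**Analysis.** Section 2.7 confines its explicit program-versus-control tests to baseline to 10 weeks. It then explores whether waiting first changes the results. If it does not, which the authors expect, a one-way repeated measures ANOVA is to estimate the program's effect size over time with more power. Pre-to-post comparisons across all participants are also allowed.

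**Discussion.** Having named short-term impact as one limitation of earlier studies, section 3 says this study will add to them, "including addressing the aforementioned limitations".

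**The concern.** An aim labelled primary tells readers what the trial is meant to answer. This one names 6 and 12 months, where the design has no untreated group. The analysis section makes the problem concrete: a single-group change over time in the pooled cohorts is to be reported as the size of the program's effect.

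That change mixes the effect of the program with whatever would have happened anyway, and the protocol gives several reasons to expect the latter not to be zero:

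- Children enter because their BMI is at or above the 85th percentile, so some regression towards the mean is likely on repeat measurement.
- Section 2.3.2 itself allows for a fall in BMI z-score among controls.
- Attrition of 30% is expected, and families who stay may differ from those who leave.
- Children grow over a year or more of follow-up, which matters most for a raw measure such as waist circumference.

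If the plan is followed as written, uncontrolled change could be published as a program effect from a randomized trial.

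**Working it through.** **1. What the stated sample size covers.** Inputs from section 2.3.2: standardized effect 0.6, 5% significance (two-sided assumed, as the article does not say), 80% power, 30% attrition. A two-sample t-test needs 45 per arm. Then 45 × 1.3 = 58.5, rounded up to 59 per arm, and 2 × 59 = 118, which is the stated total. The figure is thus reproduced from the 10-week contrast alone; no part of it relates to 6 or 12 months. (Whether multiplying by 1.3 is the right allowance for attrition is a separate question.)

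**2. Who is untreated, and when.** Weeks are counted from baseline, taking 6 months as 26 weeks and 12 months as 52. Term dates are not given, so two assumptions are shown for Cohort 2: it starts straight after the wait (week 10), or one quarter-year after Cohort 1 (52 / 4 = week 13).

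| | Untreated | Program | 6-month visit | 12-month visit |
|---|---|---|---|---|
| Cohort 1 | none | 0–10 | 10 + 26 = 36 | 10 + 52 = 62 |
| Cohort 2, start week 10 | 0–10 | 10–20 | 20 + 26 = 46 | 20 + 52 = 72 |
| Cohort 2, start week 13 | 0–13 | 13–23 | 23 + 26 = 49 | 23 + 52 = 75 |

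At week 10 the contrast is program versus no program. At every scheduled 6- and 12-month visit both cohorts have been through their program period. The number of untreated randomized comparators at those visits is 0 of 59 under either assumption.

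**3. What each later analysis in section 2.7 estimates.**

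- Cohort 1 versus Cohort 2 over time: immediate versus delayed program. This is randomized, but it is not program versus no program.
- One-way repeated measures ANOVA on the pooled cohorts: mean within-child change, equal to the program effect plus background change. Nothing in the analysis separates the two. The sentence does not list its time points, but it is the analysis offered for change over time and so the natural home of the 6- and 12-month data.
- Pre-to-post comparison of all participants: also within-group and uncontrolled.

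**4. Does the condition for pooling help?** Finding no impact of waiting means the two cohorts behave alike once treated. Both could share the same background change. Pooling makes the estimate of total change more precise; it does not remove the background part.

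**The case against.** The strongest reply is that the operative hierarchy is already right. The Abstract and sections 2.3.2 and 2.7 agree on BMI z-score over 10 weeks, the other outcomes are already secondary, and the program-versus-control tests stop at 10 weeks. The aim is one broad introductory sentence. A waitlist is a legitimate and deliberate choice, and a one-way repeated measures ANOVA is single-group by name. All of this stands. It confines the point to the wording of the aim and of the later claims, but it does not excuse calling single-group change the program's effect size.

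Three stronger readings are tempting and are not supported:

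- *The cohorts will be compared at about week 36, where full persistence would give a difference near 0 that is misread as loss of effect.* No Cohort 2 survey is scheduled then; its 6-month visit falls at about week 46 to 49. Section 2.7 also treats a null difference between cohorts as grounds for pooling, not as fading of the effect.
- *No randomized comparison survives after 10 weeks.* Immediate versus delayed program does survive; it answers a different question.
- *The Discussion claims controlled long-term evidence.* It does so at most by implication. The limitations it refers to include others, such as parent-only or child-only programs, and the Introduction describes the short-term limitation largely by length of follow-up, which a 12-month visit does extend.

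**Conclusion.** The point holds as a mismatch between the stated primary aim and what the design can identify. The aim covers five outcomes at three times; the primary outcome, test and power cover one outcome at 10 weeks; and no scheduled 6- or 12-month visit has an untreated randomized comparator. Calling the pooled repeated-measures result the program's effect size is wrong as written.

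A reader might infer that the primary analysis is compromised. It is not: the 10-week comparison and its sample size do not depend on anything after the wait. The conclusion rests on controls being offered the program as section 2.2 describes and on visits being timed from each child's own completion. It does not depend on the exact term dates. The size of the background change cannot be derived from the article, so the possible bias in the later estimates is not quantified here.

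**What to change.** 1. **Introduction, aims.** Restate the primary aim as the effect of the program versus waitlist on change in BMI z-score from baseline to 10 weeks. The other outcomes are already secondary and need no reclassification.
2. **Section 2.7.** Describe the pooled repeated-measures and pre-to-post results, including those at 6 and 12 months, as uncontrolled within-child change (maintenance after the program), and not as the program's effect size. State that finding no impact of waiting supports pooling only.
3. **Section 3.** Limit the longer-term statement to longer follow-up without a concurrent control.

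The cost is a narrower claim about lasting effectiveness. Randomization, visits, measurements and sample size stay as they are.
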